## 2.7 Secondary outcomes

Secondary outcomes and planned statistical analyses are summarised in Table 3.

**Table 3.** Secondary outcomes: summary of statistical analyses to be performed

| Analysis               | Outcome                                                                       | Groups compared             | Adjusted factors*                                   | Test                |
|------------------------|-------------------------------------------------------------------------------|-----------------------------|-----------------------------------------------------|---------------------|
| Knowledge of JE        | Number of post-intervention correct responses to nine JE knowledge statements | Intervention vs. comparator | Pre-intervention knowledge score, age, sex          | Poisson regression  |
| Intention to vaccinate | Change in participants intention to get vaccinated                            | Intervention vs. comparator | Pre-intervention intent to get vaccinated, age, sex | Logistic regression |
| Uptake of JE vaccine   | Self-reported pre-travel JE vaccine uptake                                    | Intervention vs. comparator | Post-intervention intention to vaccinate, age, sex  | Logistic regression |

## 2.8. Secondary Outcome 1: JE knowledge

*Null hypothesis:* An online JE vaccine decision aid does not lead to a greater improvement in participants' knowledge of JE compared to standard online health information (HealthDirect fact sheet) among Australian adults planning overseas travel to JE risk areas.

*Research question:* Does use of JEVaDA lead to a greater increase in participants' knowledge of JE compared to standard online health information (HealthDirect fact sheet) among Australian adults planning overseas travel to JE risk areas?

Knowledge of JE will be assessed by the change in the proportion of correct responses to a set of nine JE knowledge statements from pre- to post-intervention. Participants will respond to the same nine statements at both time points, indicating whether they believe each statement is true, false or not sure (see Table 4). Responses will be coded numerically, and the total number of correct responses will be calculated for each participant at baseline and post intervention.

**Table 4.** JE knowledge statements

| Statements                                                                                             | True | False | Not sure |
|--------------------------------------------------------------------------------------------------------|------|-------|----------|
| You can catch JE from another person                                                                   |      | X     |          |
| JE is spread by mosquito bites                                                                         | X    |       |          |
| JE can be serious: some people may die from it, and some who survive will have long-term health issues | X    |       |          |
| There is a specific treatment that can help your body fight JE                                         |      | X     |          |
| JE can be prevented                                                                                    | X    |       |          |
| JE is caused by a bacteria                                                                             |      | X     |          |
| JE is a common disease in travellers to Asia                                                           |      | X     |          |
| Two vaccines for JE are available in Australia                                                         | X    |       |          |
| Avoiding mosquito bites can lower your risk of getting JE                                              | X    |       |          |

*NB: Correct answers are indicated with red crosses*

This secondary outcome will be analysed using Poisson regression. The dependent variable will be the post-intervention knowledge score (number of correct responses), with the number of questions included as an offset. The pre-intervention knowledge score (number of correct responses), along with age and sex will be included as covariates to adjust for baseline differences. Findings will be reported as incidence rate ratios (IRRs) with 95% confidence intervals (CIs) and p-values (Table 5).

**Table 5.** Poisson regression analysis of JE knowledge

| Variable                              | Incidence rate ratio | 95% CI | p-value |
|---------------------------------------|----------------------|--------|---------|
| Intervention group (reference=JEVaDA) |                      |        |         |
| Pre-intervention knowledge score      |                      |        |         |
| Age                                   |                      |        |         |
| Female sex                            |                      |        |         |

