### 5.7.2. SECONDARY OUTCOMES

#### Knowledge

Knowledge of JE will be assessed at the individual level by comparing participants' responses to 9 knowledge statements about JE in the pre- and post-intervention surveys. Participants will be asked to indicate whether they believe each statement true, false or if they are not sure. Responses will be categorised as correct (where participants correctly identify a true statement as true or a false statement as false), incorrect (where participants incorrectly identify a true statement as false or a false statement as true), or "not sure" responses. The secondary outcome will be the change in the proportion of correct responses from pre- to post-intervention, with the difference in knowledge gains compared between the intervention and control groups.

Similar to other decision aid evaluation studies,(21-23) these knowledge questions have been developed specifically for this study, based on the content presented in the decision aid, and

knowledge considered important in the literature. The statements have been reviewed and refined with input from both clinicians and consumers to ensure accuracy and relevance.

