| JE is spread by mosquito bites                                                                         | X    |       |          |
| JE can be serious: some people may die from it, and some who survive will have long-term health issues | X    |       |          |
| There is a specific treatment that can help your body fight JE                                         |      | X     |          |
| JE can be prevented                                                                                    | X    |       |          |
| JE is caused by a bacteria                                                                             |      | X     |          |
| Most travellers to JE risk areas don't get JE                                                          | X    |       |          |
| Two vaccines for JE are available in Australia                                                         | X    |       |          |
| Avoiding mosquito bites can lower your risk of getting JE                                              | X    |       |          |

760 NB: Correct answers are indicated with red crosses

761

762

763 How concerned are you about getting JE on your upcoming trip?

- 764 ☐ Not at all concerned
- 765 ☐ A little concerned
- 766 ☐ Moderately concerned
- 767 ☐ Very concerned

768

769

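### Knowledge item 7 has different wording and the opposite correct answer in SAP Table 4 and in the Appendix 4 surveys, so the SAP's only answer key does not match the printed instrument

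*Combined protocol and SAP*

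**What the plan says.** Protocol 5.7.2 (Knowledge) bases the outcome on "participants' responses to 9 knowledge statements about JE in the pre- and post-intervention surveys". It defines a correct response as one "where participants correctly identify a true statement as true or a false statement as false", and keeps not-sure answers as a separate category.

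Appendix 4 prints the nine statements twice, once in each questionnaire. The seventh is "Most travellers to JE risk areas don't get JE" both times, with the mark under True.

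SAP 2.8 says "Participants will respond to the same nine statements at both time points" and points to Table 4 for them. There the seventh statement is "JE is a common disease in travellers to Asia", with the mark under False. The note under the table says "Correct answers are indicated with red crosses", so Table 4 is an answer key as well as a list, and it is the only key in the SAP.

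The score is then built and used as follows: "the total number of correct responses will be calculated for each participant at baseline and post intervention". For the model, "The dependent variable will be the post-intervention knowledge score (number of correct responses), with the number of questions included as an offset". The pre-intervention score enters as a covariate with age and sex.

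Neither the protocol's document history nor SAP Section 3 mentions a replaced or reworded knowledge item.

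**The concern.** Two current documents give different accounts of one of the nine items that make up a prespecified secondary outcome. The two statements are not restatements of each other. A disease could be called common even though most travellers never catch it, so they are different questions and may differ in difficulty.

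An analyst who takes the key from Table 4 and applies it row by row to data collected with Appendix 4 would mark the right answer to item 7 wrong and the wrong answer right. The total would still run from 0 to 9, so a range check would not reveal it.

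Item 7 is also the only statement about how likely travellers are to get JE. Protocol 3.2 describes JEVaDA as helping travellers understand risks, so responses to this item may well differ between arms. In that case a scoring error would not cancel. Even with correct code, a report that reproduces the wrong list would describe a question nobody was asked.

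**Working it through.** **Step 1. Compare the keys.** Inputs: the marked columns in the two Appendix 4 questionnaires and in SAP Table 4, items 1 to 9 in printed order.

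| Source | Key | True | False |
|---|---|---|---|
| Appendix 4, pre-intervention | F T T F T F **T** T T | 6 | 3 |
| Appendix 4, post-intervention | F T T F T F **T** T T | 6 | 3 |
| SAP Table 4 | F T T F T F **F** T T | 5 | 4 |

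All three lists have nine items, as the protocol and SAP state. They differ at item 7 only. There both the wording and the marked column differ, and each mark fits its own statement, so a table column displaced in text extraction does not explain it.

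**Step 2. Score Appendix 4 answers by the Table 4 key, by position.** Other eight items correct:

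| Answer to item 7 | Survey key | Table 4 key |
|---|---|---|
| True | 9 | 8 |
| False | 8 | 9 |
| Not sure | 8 | 8 |

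The largest shift is 1 item, 1/9 = 11.1 percentage points, per person per time point. A participant who moves from False to True gains one item but would be recorded as losing one.

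**Step 3. Effect on the arm comparison.** Let M be an arm's mean on the other eight items, and t and f the proportions answering True and False to item 7. The arm mean is M + t under the survey key and M + f under the reversed key. With Δ meaning JEVaDA minus control, the difference in means changes from ΔM + Δt to ΔM + Δf.

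The documents give no item-level rates, so every rate and every M below is an assumption:

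| M control / JEVaDA | t, f control | t, f JEVaDA | Difference: right → reversed | Ratio of means: right → reversed |
|---|---|---|---|---|
| 6.0 / 6.5 | 0.60, 0.20 | 0.60, 0.20 | 0.50 → 0.50 | 1.076 → 1.081 |
| 6.0 / 6.5 | 0.60, 0.20 | 0.75, 0.15 | 0.65 → 0.45 | 1.098 → 1.073 |
| 6.0 / 6.5 | 0.50, 0.25 | 0.80, 0.10 | 0.80 → 0.35 | 1.123 → 1.056 |
| 6.0 / 6.3 | 0.60, 0.20 | 0.80, 0.10 | 0.50 → 0.20 | 1.076 → 1.032 |
| 6.0 / 6.0 | 0.60, 0.20 | 0.80, 0.10 | 0.20 → −0.10 | 1.030 → 0.984 |

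Last row in full: 6.80/6.60 = 1.030 and 6.10/6.20 = 0.984.

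When JEVaDA does better on item 7 (Δt > 0, Δf < 0), the direction changes only if the advantage on the other eight items is smaller than the fall in False answers, that is, ΔM < −Δf. In the last two rows −Δf = 0.10, so ΔM = 0 changes direction and ΔM = 0.3 does not.

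**Step 4. Precision in the direction-change case.** Take 175 per arm (SAP 2.5) and model-based Poisson errors, ignoring covariates. SE of the log ratio = √(1/(175 × 6.60) + 1/(175 × 6.80)) = 0.041, so 1.03 has a 95% interval of about 0.95 to 1.12. With 6.20 and 6.10 the SE is 0.043, and 0.98 has an interval of about 0.90 to 1.07. Both include 1.

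**The case against.** The best reply is that nothing here shows a score has been or will be miscalculated. Each key is right for the statement printed beside it. Protocol 5.7.2 scores by whether the statement shown is true or false, not by row, and SAP 2.8 does not prescribe scoring by row. Reversal needs two things that are not documented: that the Appendix 4 wording was fielded, and that the Table 4 key was applied to it without reading the statement. If the Table 4 wording was fielded, its key is correct and Appendix 4 is what needs amending. All of this stands.

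Three further limits also stand. The size rests on assumed rates. The example that changes direction assumes no arm difference on the other eight items, and in Step 4 both estimates are compatible with no effect. The baseline score is collected before randomisation, so mis-scoring it is expected to affect both arms alike. That weakens the adjustment slightly but does not itself bias the comparison.

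A reader might infer from the two tables that the SAP's scoring is wrong, or that the knowledge result will be reversed. The documents support neither, because they do not say which wording was fielded.

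The reply does not remove the contradiction. The semantic rule in the protocol helps only someone who knows which statement was shown, and the SAP says it was the one in Table 4. Neither list is marked superseded: protocol version 2 (17/11/2025), which carries the Appendix 4 wording, is dated four days after SAP version 3.1 (13-Nov-2025).

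**Conclusion.** The concern holds as a contradiction between the instrument and the answer key. Item 7 differs in wording and in correct answer, and one document misstates what participants were asked.

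The consequence for scoring is conditional. If Appendix 4 was fielded and Table 4 is applied by position, True and False answers to item 7 swap, worth up to 1 of 9 per participant per time point. Under the assumed rates in the working, the between-arm difference ranges from unchanged (0.50 → 0.50), through attenuated (0.80 → 0.35), to a small change of sign (0.20 → −0.10). These figures are illustrative and are not a forecast. If item 7 is keyed to the statement actually shown, the effect is zero.

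Only the knowledge outcome is affected. The DCS primary outcome, the sample size, intention and uptake do not use this score. Because the surveys collect True, False or not sure for each statement, any mis-scoring can be undone from the raw responses. Should-fix.

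**What to change.** 1. Confirm from the REDCap build the item 7 wording that was fielded, separately for the pre- and post-intervention surveys.
2. Make SAP Table 4 and both Appendix 4 questionnaires identical to it. If the two surveys used different wording, say so, and correct the SAP's statement that the same nine items were used.
3. Score item 7 by the key for the wording shown: True is correct for the Appendix 4 statement, False for the Table 4 statement. Tie the key to the item text in the scoring code, not to row position.
4. Record the correction in SAP Section 3, stating whether any scoring done so far used the right key. Rescore from the raw responses if it did not.

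The cost is one table row, one check of the scoring code and one log entry. No new data and no change of model are needed.

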## 2.9 Secondary Outcome 2: Intention to vaccinate

*Null hypothesis:* The online JE vaccine decision aid (JEVaDA) does not lead to a greater increase in participants' intention to get vaccinated before their trip compared to standard online health information among Australian adults planning overseas travel to JE risk areas.

*Research question:* Does use of JEVaDA lead to a greater increase in participants' intention to get vaccinated before their trip compared to standard online health information among Australian adults planning overseas travel to JE risk areas?

Intention to vaccinate will be assessed by the change in response to the question "Do you want to get a JE vaccine before your upcoming trip?". This question will be asked in both the pre-intervention and post-intervention surveys. Response options include: "No, I do not want to", "Yes, I

do want to”, “I am not sure”, and “I am already vaccinated”. For analysis, responses will be recoded into a binary variable, where “Yes, I do want to” is coded as 1, and all other responses are coded as 0. A new binary outcome variable will be created to capture positive change, defined as a shift from 0 pre-intervention to 1 post-intervention.

This outcome will be analysed using multivariable logistic regression. The dependent variable will be whether participants demonstrated a positive change in intention to vaccinate, and the primary independent variable will be group allocation. Baseline (pre-intervention) intention to vaccinate, age and sex will be included as covariates to adjust for baseline differences. Findings will be reported as adjusted odds ratios (ORs) with 95% confidence intervals (CIs) and p-values to indicate the strength and significance of the associations (Table 6).

**Table 6.** Logistic regression analysis of intention to vaccinate

| Variable                                 | Adjusted odds ratio (aOR) | 95% CI | p-value |
|------------------------------------------|---------------------------|--------|---------|
| Intervention group
(reference=JEVaDA) |                           |        |         |
| Baseline intention to
vaccinate       |                           |        |         |
| Age                                      |                           |        |         |
| Female sex                               |                           |        |         |

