### **Intention to vaccinate**

Intention to vaccinate will be assessed by comparing participants' responses to the question "Do you want to get a JE vaccine before your upcoming trip?" in both the pre- and post-intervention surveys. This question is based on the WHO's Behaviour and social drivers of vaccination survey priority questions. Responses will be categorised into four groups: 1) those who don't want to get vaccinated, 2) those who are not sure, 3) those who intend to get vaccinated and 4) those who are already vaccinated. The primary outcome will be the change in the proportion of participants who express an intention to get vaccinated before their trip, comparing the intervention group to the control group.

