## Section 2: Statistical analysis

### 2.1 Confidence intervals and p-values

For all statistical tests, a significance level of 5% will be employed (p value 0.05) and 95% confidence intervals will be reported.

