## 2.5 Sample size analysis

Sample size estimates are based on detecting an effect size of 0.30 for the primary outcome, as recommended in the DCS User Manual [3]. Using the ANCOVA approach and assuming a modest correlation of 0.5 between pre and post-intervention DCS scores within-participant, we will have over 90% power (2-sided significance level of 0.05) to detect an effect size of 0.30 in the primary outcome with a sample size of approximately 175 participants per group (total 350 patients). Target recruitment was set at 500 participants to account for a 30% non-completion rate. The effect size is the difference in post-intervention DCS scores between intervention and comparator, adjusted for pre-intervention DCS score, and expressed as a fraction of the standard deviation of pre-intervention DCS scores.

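### SAP 2.9: with intention coded as Yes versus everything else, the baseline covariate is constant among all participants who can show the outcome, so No and Not sure go unadjusted

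*Combined protocol and SAP*

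**What the plan says.** The question on wanting a JE vaccine before the trip is asked in both surveys, with the answers No, Yes, Not sure and Already vaccinated (protocol Appendix 4). Protocol 5.7.2 says "Responses will be categorised into four groups", and in the same paragraph takes as its outcome the change in the proportion intending to be vaccinated.

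SAP 2.9 recodes the answers: Yes "is coded as 1, and all other responses are coded as 0". The outcome is a new binary variable that equals 1 only when a participant goes from code 0 before to code 1 after. It is analysed by logistic regression on allocation. Baseline intention, "age and sex will be included as covariates to adjust for baseline differences". Neither the text nor Table 3 says how many levels baseline intention has; Table 6 gives it a single row. The SAP plans no transition table, ordinal analysis or sensitivity analysis for this outcome, and states no power for it.

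**The concern.** A baseline covariate is useful when it separates participants with different chances of the outcome. Here the split that matters is between people who start at No and people who start at Not sure, since their chances of ending at Yes are likely to differ a good deal. The recode gives both groups the same value. Randomisation is stratified by age group, gender and state or territory (protocol 5.2), not by intention, so a chance difference between arms in that mix would go uncorrected. The treatment comparison would also be less precise than the data allow. The information needed to avoid this is already collected.

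**Working it through.** **1. The plan's own figure.** SAP 2.5 covers the primary outcome only: "detecting an effect size of 0.30 for the primary outcome", "assuming a modest correlation of 0.5 between pre and post-intervention DCS scores within-participant", "over 90% power (2-sided significance level of 0.05", with "approximately 175 participants per group (total 350 patients". Per arm, n = 2(z₀.₉₇₅ + z₀.₉₀)²(1 − ρ²)/δ² = 2 × (1.960 + 1.282)² × 0.75/0.09 = 175.1, rounded up to 176. Power at 175 per arm is 89.98%, and 350/0.7 = 500. The figure reproduces to rounding. Below, only the 175 per arm and the 5% level (SAP 2.1) come from the documents. All intention rates and effects are assumptions.

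**2. What the coding does.**

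| Baseline answer | Baseline code | Possible outcome values |
|---|---|---|
| No | 0 | 0 or 1 |
| Not sure | 0 | 0 or 1 |
| Already vaccinated | 0 | 0 or 1 in form |
| Yes | 1 | 0 only |

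Among baseline-Yes participants every outcome is 0. The likelihood keeps rising as their coefficient goes to minus infinity, so the Table 6 odds ratio for baseline intention cannot be estimated and these participants add nothing to the treatment comparison. In the rows that remain, the 0/1 covariate equals 0 throughout and cannot adjust for anything.

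**3. Chance imbalance with no treatment effect.** Assume baseline No/Not sure/Yes of 30/45/25%. Non-Yes participants per arm: 0.75 × 175 ≈ 131. Not-sure share among them: 45/75 = 60%. The SD of the between-arm difference in that share is √(2 × 0.6 × 0.4/131) = 0.0605. A 10-point difference is 0.10/0.0605 = 1.65 SD, two-sided probability about 0.10.

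Take shares of 55% and 65%, a 26.9% chance of ending at Yes from Not sure, and three chances from No:

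| Chance of Yes from No | Proportion at Yes, 55% arm | Proportion at Yes, 65% arm | Null OR |
|---|---|---|---|
| 11.9% | 0.202 | 0.217 | 1.09 |
| 4.7% | 0.169 | 0.191 | 1.16 |
| 1.8% | 0.156 | 0.181 | 1.20 |

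For the last row: 0.55 × 0.269 + 0.45 × 0.018 = 0.156; 0.65 × 0.269 + 0.35 × 0.018 = 0.181; OR = (0.181/0.819)/(0.156/0.844) = 1.20.

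**4. Power, central case.** Assumed baseline No/Not sure/Yes/Already of 25/40/30/5%. Assumed control-arm chances of ending at No/Not sure/Yes: 60/27/13% from No, 20/45/35% from Not sure, 5/10/85% from Yes. The treatment OR is 1.8 at both cut-points. There were 2,000 simulated trials, with all tests run on the same trials; the standard error of one power figure near 50% is √(0.25/2000) = 1.1 points.

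| Analysis | Power | Step |
|---|---|---|
| SAP outcome, 0/1 baseline | 45.0% | – |
| SAP outcome, recorded baseline categories | 48.8% | +3.8 |
| Post-intervention Yes in everyone, recorded categories | 57.2% | +8.4 |
| Ordinal, already vaccinated excluded | 68.2% | +11.0 |

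Fitted logistic and proportional-odds models with age and sex (300 trials) gave 46% for the first row and 70% for the last.

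**5. Range for the baseline categories alone.**
- Twelve scenarios with two baseline mixes, two sets of control rates, OR 1.8 and three patterns in which Yes is affected: +1.3 to +4.6 points.
- A second set with four other mixes, the chances in step 3 and OR 1.8 or 2.2: about +1 to +8 for the SAP outcome and +0.5 to +6 for post-intervention Yes. Largest example (40/40/20%, 1.8% from No, OR 2.2): 55.9% to 63.4%, and 64.0% to 70.2%.
- Over all the assumed rates tried, the gain for the SAP outcome was about +1 to +10 points. Type I error stayed near 5%.

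**6. Ordinal analysis against the SAP outcome, OR 1.8, by where the aid acts.**

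| Effect | SAP outcome | Ordinal |
|---|---|---|
| Whole scale | 35–54% | 62–77% |
| Not sure/Yes boundary only | 34–53% | 19–32% |
| Yes gains proportionally from No and Not sure | 35–51% | 28–50% |
| No/Not sure boundary only | about 5% | 18–30% |

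**The case against.** A reader might infer that the SAP departs from the protocol by collapsing four groups to two, that it hides No-to-Not-sure movement, and that power is therefore lost. The documents do not support that. Protocol 5.7.2 lists four groups but defines the outcome as the proportion intending to be vaccinated, and protocol 3.1 describes intention as planning to be vaccinated before travel. Movement from No to Not sure lies outside that endpoint. An ordinal analysis answers a different question, and step 6 shows that it has less power when the aid acts only at the step to Yes. Its 23-point advantage in the central case is also a mixture: 8.4 points come from replacing the 0-to-1 shift outcome and 3.8 from the baseline categories.

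On the baseline covariate, the best reply is that the SAP never says it is binary. The single row in Table 6 is weak evidence, since sex also has one row there while Table 1 separates female and non-binary. The reply has some force, but the recode sentence follows directly on a description of the question in both surveys, and if categories are intended the text still has to say so. It is also fair that randomisation balances the mix on average, that type I error is unaffected, and that a 10-point imbalance is uncommon. Those facts limit the size of the problem without making the adjustment work.

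**Conclusion.** The point holds for the baseline covariate. As SAP 2.9 is most naturally read, baseline intention is constant among everyone who can show the outcome, and the stated adjustment for baseline differences has no effect. The cost is modest: about 1 to 10 points of power under the assumed rates, most when few people starting at No move to Yes, and a null odds ratio of 1.09 to 1.20 in the roughly 1 trial in 10 with a 10-point imbalance. These sizes rest on assumed intention rates and on odds ratios of 1.8 to 2.2; the documents supply only the number per arm and the significance level. Yes versus the rest is not itself an error, and a general loss of power from collapsing the scale is not shown. Severity is minor: the outcome is secondary and no power is claimed for it.

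**What to change.** In SAP 2.9 and Tables 3 and 6, enter baseline intention as its recorded categories (No, Not sure, Yes, Already vaccinated), or state that already-vaccinated participants are excluded from this analysis. Make post-intervention Yes the dependent variable. If the 0-to-1 shift is kept, the odds ratio for baseline Yes still cannot be estimated.

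Optional, and supportive only: a No/Not sure/Yes transition table by arm, and a proportional-odds model without the already vaccinated, adjusted for baseline category, age and sex. It should not replace the Yes analysis, because it relies on proportional odds and loses power if the aid acts only at the Yes boundary.

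The cost is SAP wording and one or two extra parameters, with no new data. SAP Section 3 describes Version 3 (3 March 2025) as final before analysis, so if the data have since been analysed, the additions should be labelled post hoc.

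### SAP 2.9 counts only gains in intention and adjusts for a baseline answer that rules the outcome out, so it compares baseline non-intenders only and does not measure the protocol's change in proportion

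*Combined protocol and SAP*

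**What the plan says.** SAP 2.9 reduces the four answers on wanting a JE vaccine to two. Yes is 1, "and all other responses are coded as 0", which groups No, not sure and already vaccinated. From the pre and post values it builds one binary outcome for positive change, "defined as a shift from 0 pre-intervention to 1 post-intervention".

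The model is a logistic regression of that outcome on group. On the other terms the SAP says: "Baseline (pre-intervention) intention to vaccinate, age and sex will be included as covariates to adjust for baseline differences". SAP Table 3 repeats the set ("Pre-intervention intent to get vaccinated, age, sex"), and SAP Table 6 reserves a row for the odds ratio, confidence interval and p-value of baseline intention.

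Protocol 5.7.2 defines the same secondary outcome as "the change in the proportion of participants who express an intention to get vaccinated before their trip, comparing the intervention group to the control group". SAP 1.3 says the secondary outcomes are analysed in the ITT and modified ITT populations. Neither is limited by the baseline answer.

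**The concern.** The outcome and the covariate overlap by construction. The baseline answer is part of the outcome's definition, and one of its two values makes the outcome impossible. Three things follow.

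- One planned line of Table 6 cannot be produced.
- The group comparison rests on fewer people than the populations in SAP 1.3, and a reader of the SAP would not know it.
- A participant who wanted the vaccine and no longer does is scored like one who never changed. The SAP therefore measures gains, while the protocol's proportion nets gains against losses.

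The last matters most. Increased intention is a named hypothesis (protocol 3.1). JEVaDA sets out risks, benefits and trade-offs and asks users to weigh them against their values (protocol 3.2 and 4.1). Such a tool could move some people away from vaccination as well as towards it.

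**Working it through.** **Inputs.** The coding, outcome and covariates are from SAP 2.9. The analysed number, 350 (175 per group), is from SAP 2.5, which sizes the trial for the primary outcome (500 × 0.70 = 350). The documents state no power, baseline share, gain rate or loss rate for intention, so every rate below is assumed.

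**Step 1: the outcome (Y) by definition.**

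| Pre | Post | Y |
|---|---|---|
| 0 | 0 | 0 |
| 0 | 1 | 1 |
| 1 | 1 | 0 |
| 1 | 0 | 0 |

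The cell with pre = 1 and Y = 1 is always empty. The cell with pre = 0 is free to hold either value. This is quasi-complete separation, and it depends on no assumed rate.

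**Step 2: what the model then estimates.** Let γ be the coefficient of baseline intention. A baseline-Yes participant contributes −log(1 + exp(η + γ)) to the log-likelihood, where η collects the other terms. This rises towards 0 as γ falls without limit, so no finite γ maximises it. In the limit these participants contribute nothing, and the likelihood that remains is that of the baseline = 0 stratum.

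**Step 3: numerical check.** Simulated data, 175 per arm. Assumed gains among non-intenders were 40% vs 30% (JEVaDA vs control), with 85% of baseline intenders still saying Yes in both arms. The baseline-Yes share was set at 20%, 40% and 60%; the simulated counts were 87, 130 and 218 of 350. At the 40% setting:

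| Iterations | Baseline coefficient (SE) | Group coefficient (SE) |
|---|---|---|
| 8 | −9.02 (6.3) | 0.3512 (0.2829) |
| 15 | −16.02 (209.5) | 0.3512 (0.283) |
| 35 | −36.02 (about 4.6 million) | 0.3512 (0.283) |

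A fit restricted to baseline = 0 (n = 220) gives the same group coefficient, 0.3512 (SE 0.283). The pattern is the same at the other two settings, where 263 and 132 of the 350 contribute.

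**Step 4: the effect of ignoring losses.** Let p be the baseline-Yes share, g the gain rate among non-intenders and l the loss rate among intenders. The post-intervention proportion is p(1 − l) + (1 − p)g. Assume p = 0.40, g = 0.25 vs 0.15 and l = 0.20 vs 0.05 (JEVaDA vs control).

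- Control: 0.40 × 0.95 + 0.60 × 0.15 = 0.47
- JEVaDA: 0.40 × 0.80 + 0.60 × 0.25 = 0.47
- SAP odds ratio, JEVaDA vs control: (0.25/0.75)/(0.15/0.85) = 1.89

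Table 6 takes JEVaDA as the reference, so it would print the reciprocal, 1/1.89 = 0.53.

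**Step 5: sensitivity to the assumed loss rate.** Other inputs are unchanged and control stays at 47%.

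| JEVaDA loss rate | JEVaDA post-intervention Yes |
|---|---|
| 5% | 0.40 × 0.95 + 0.15 = 53% |
| 10% | 0.40 × 0.90 + 0.15 = 51% |
| 15% | 0.40 × 0.85 + 0.15 = 49% |
| 20% | 0.40 × 0.80 + 0.15 = 47% |

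The SAP odds ratio is 1.89 in every row.

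**Step 6: a reversal is also possible.** Assume 175 per arm with 70 Yes at baseline in each; JEVaDA 30 gains and 30 losses, control 20 gains and 5 losses. The SAP odds ratio is (30/75)/(20/85) = 1.70. Post-intervention Yes is 70 vs 85, with unadjusted odds ratio (70/105)/(85/90) = 0.71.

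**Step 7: the alternative model.** Regressing post-intervention intention on group, baseline intention, age and sex converged at all three settings of Step 3. The baseline coefficients were finite (1.79, 2.16 and 2.69; SE 0.27 to 0.28) and all 350 participants contributed. In the Step 4 example this model, without age and sex, gives a group odds ratio of exactly 1.00. With no group effect the fitted proportions are 0.875 for intenders and 0.20 for non-intenders, and 0.40 × 0.875 + 0.60 × 0.20 = 0.47 matches both arms.

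**The case against.** The strongest reply is that the treatment comparison survives. A reader might infer from the separation that the model cannot be fitted at all. That does not follow: separation is in one direction only, the group coefficient is finite and stable, and only the baseline-intention coefficient runs away. What StataBE 18 would display was not tested, and no failure is claimed for it.

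A reader might also infer that an unstated subgroup means a biased contrast. The documents do not support that. Baseline intention is asked in the pre-intervention survey, before allocation (protocol 4 and 5.2), so the comparison among baseline non-intenders remains a randomised one. The harm is an undeclared restriction and a smaller number, not an invalid comparison.

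Third, counting gains only can be a deliberate choice of question, and SAP 2.9 says openly that the variable captures positive change. This stands in part. A gains-only question is legitimate, but it is not the protocol's "change in the proportion of participants who express an intention to get vaccinated before their trip", and the SAP's list of changes records no decision to redefine the outcome.

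Finally, the example in Step 4 needs losses four times as frequent under JEVaDA as under control. That is fair: it shows what can happen, not what is likely.

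**Conclusion.** The point holds, on the SAP's definitions alone, in three parts: the baseline-intention odds ratio in Table 6 is not estimable; the group odds ratio describes only baseline non-intenders, which the SAP does not say; and losses of intention are scored as no change, so the analysis does not answer protocol 5.7.2.

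The size is conditional. The planned analysis can favour JEVaDA when the proportion wanting the vaccine is equal (1.89 against 47% in both arms) or lower (1.70 against 0.71), but only if losses are sufficiently more frequent under JEVaDA. In the main example, the direction agrees once JEVaDA losses are 15% or less. The number contributing likewise depends on the unknown baseline share.

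A reader might go further and expect the trial's conclusion on intention to be wrong. Nothing in the documents shows that, since they give no gain or loss rates. The matter is confined to one of the three secondary outcomes in SAP Table 3; the primary analysis and its sample size are unaffected.

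**What to change.** In SAP 2.9 and Table 3, make post-intervention intention (Yes = 1, otherwise 0) the dependent variable of the logistic regression, with group, baseline intention, age and sex as covariates. This is the structure SAP 2.6 uses for decisional conflict and SAP 2.8 for knowledge. The rows of Table 6 can stay, and all of them become estimable. Add a pre/post transition table by arm so that gains and losses are both visible. Entering baseline intention as four categories under the present outcome would not help, because the Yes category would still contain no events.

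If the gains-only question is wanted as well, report it as supplementary, labelled as restricted to baseline non-intenders and without the baseline covariate.

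The change uses the same data, software and model family. The cost depends on timing. SAP Section 3 describes Version 3 (3 March 2025) as the final plan before data analysis. If analysis has begun, replacing the dependent variable must be dated and disclosed as an SAP amendment, and the currently planned 0-to-1 analysis should then be reported as the supplementary one just described.
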